### **7.4 Subject Data Protection**

The Investigator is responsible for keeping a list of all subjects (who have been allocated subject numbers) including subject numbers, full names (of parent and child, if applicable) and parent addresses.

The parents/guardians should also be informed in writing and agree to the possibility of audits and /or monitoring by authorized representatives of the Sponsor, the manufacturer of the study drug, and/or regulatory authorities in which case a review of those parts of the laboratory records relevant to the study may be required.

The parents/guardians should be informed in writing and agree to that the results will be stored and analyzed in a computer, maintaining confidentiality in accordance with Swedish data laws and “Personuppgiftslagen” (PUL SFS 1998:204, SFS 1998:1191)

## 7.5 Biobank

Samples taken in this study will be stored in a biobank according to the Swedish biobank law ((SFS 2002:297). The biobank is registred at the national board of health and welfare in Sweden (Socialstyrelsen). Samples will be thrown away when the study is finished. No further analyses other than those specified in this protocol will be performed on the samples. The parents will be informed about this.

## 8 STUDY EVALUATIONS

### 8.1 Efficacy evaluations

All values obtained from efficacy evaluations should be recorded onto the case record form (CRF). Serum samples will be taken simultaneously with clinical blood sampling.

#### Fatty acid analyses

All laboratory values for clinical chemistry will be obtained from Klinisk kemi, Sahlgrenska Universitetssjukhuset, the accredited central laboratory at Sahlgrenska / Östra hospital, SWEDAC accreditation number 1240 according to their routines.

The analyses of fatty acids will be performed by [name] laboratory at the Göteborg University /SU Östra.

Total lipids of serum will be extracted according to Folch et al. [10]. Serum phospholipids will be fractionated on a single SEP-PAK aminopropyl cartridge (Waters Corp., Massachusetts, USA) and eluted with methanol after washing with chloroform:isopropanol 2:1 and 2% HAc in ether. The fraction of lipids will be transmethyalted in methanolic-HCL-3N at 80°C over 4 hours. The FA methyl esters will be separated by capillary gas-liquid chromatography in a Hewlett-Packard 6890 gas chromatograph equipped with a 30 m x 0.25 mm SP-2380 column; film thickness 20 µm. Helium at 1.4 ml/min will be used as carrier gas. The injector and detector temperatures will be 250°C. The column oven temperature is programmed from 60°C to 230°C at a heating rate of 8°C/min up to 155°C, 1.5°C/min up to 180°C and thereafter 6°C/min up to 230°C, where it is ran for 10 min. The separation will be recorded with HP GC Chem Station software (HP GC, Wilmington, DE). Heneicosanoic acid (21:0) will be used as internal standard and the FA methyl esters identified by comparison with retention times of pure reference substances (Sigma Aldrich Sweden AB, Stockholm, Sweden). The method has been described earlier (ref Peng YM, Zhang TY, Wang Q, Zetterström R, Strandvik B. Fatty acid composition in breast milk and serum phospholipids of healthy term Chinese infants during first 6 weeks of life. *Acta Paediatr* 2007;96: 1640-5).

#### ROP examination

The retinal examination will be performed once weekly starting at five to six weeks of age according to a standardized protocol and to clinical screening praxis. The ophthalmologic assessment will be performed with strict criteria according to general Swedish Guidelines issued by the Swedish Ophthalmological Society: The Guidelines are available at following link: [www.swedeye.org/SOTA/rop/SOTA-ROP\\_2006.pdf](http://www.swedeye.org/SOTA/rop/SOTA-ROP_2006.pdf).

**Growth**

Length, weight and head circumference will be registered weekly from birth until 40 weeks postmenstrual age and at 2.5 and 6 years.

**Neurologic development**

Cranial ultrasound will be performed according to clinical praxis. MRI of the brain will be performed at 40 weeks PMA.

At 2.5 years a clinical examination including neurologic evaluation (neurologist) cognitive evaluation with Bailey-test (psychologist) and ophthalmologic examination will be performed.

At 6 years a clinical examination including neurologic evaluation (neurologist) cognitive evaluation with WPPSI alt WISC, short visuo-motor test and a behavioral test and extensive ophthalmologic examination, including visual perception and morphologic and functional examination of the retina, will be performed.

**8.2 Safety Evaluations**

All values obtained from safety evaluations should be recorded onto the CRF. Safety evaluations consist of the following:

- **AE reporting:** include SAEs and AEs recorded starting from receiving informed consent until the final study examination / sampling. AE reporting is further outlined in section 9, Safety.
- **Physical examination:** A complete physical examination will be performed in all subjects at birth according to standard clinical routines.
- **Vital signs:** Heart rate, blood pressure, pO2 and breath frequency will be monitored from birth throughout the study. Subjects are connected with continuous surveillance of heart beat, breath frequency and pO2. An alarm will notify the personnel and if any true divergences have occurred, these will be recorded in the patient record and in the CRF. Children with artery catheter are always under continuous intra artery blood pressure control with alarm for any irregular episodes.
- **Retinal exam:** Retinal exam will be performed according to clinical screening protocol. Any deviations from normal will be described in the CRF.
- **Cranial/Cerebral ultrasound** will be performed in all subjects by a pediatric radiologist as clinical routine. Any deviations from normal will be described in the CRF.
- **Magnetic resonance imaging of the brain** will be performed in all subjects by a pediatric radiologist as clinical routine. Any deviations from normal will be described in the CRF.
- **Laboratory evaluations:** Laboratory assessments will be performed according to standard clinical routines. Blood samples for fatty acid analyses; 0.2 ml from the child will be taken according to present clinical practice at days 1, 7 and 14 and in postmenstrual weeks 28, 32, 36 and 40. At the same time (except from day 1), breast milk samples are taken and length, weight and head circumference are measured.

Blood samples from the mothers for FA analyses will be taken after birth, day 7 and at gestational weeks 36 and 40.

Analyses of triglycerides cannot be taken more frequently than described in the protocol as the small circulating blood volume of these very preterm infants will not allow more sampling than what is already specified in the protocol.

It is extremely rare in our neonatal intensive care unit that a WLBW infant is planned to receive more than 2 g fat/kg/24 h intravenously, but if it should happen the infant is always very thoroughly followed by clinical checkups with daily measurements of plasma triglycerides and blood gases (as a safety control of metabolic state).

***Laboratory evaluations consist of:***

**Hematology:** Hemoglobin, hematocrit and platelets.

**Chemistry:** Sodium, potassium, calcium, uric acid, creatinine, alkaline phosphatase, albumin, total bilirubin, AST, ALT.

**Plasma glucose:** Blood for measurement of p-glucose is obtained from routine daily blood gas measurements and will be recorded in the CRF throughout the study.

### **8.3 Other Evaluations**

- **Maternal and perinatal history:** Maternal and perinatal history will be recorded as soon as possible after birth after questioning the subject's parents and/or recorded from the mother's patient record for the pregnancy ("Förlossningsjournaler" FHV-1 and FHV-2).
- **Weight, Length and Head Circumference (HC):** Weight, length and HC of the subject will be recorded once weekly from birth to 40 postmenstrual weeks and at 2.5 and 6 years.

## **9 SAFETY**

### **9.1 Recording Adverse Events**

Adverse events must be recorded starting from the time of informed consent until the final study examination / sampling day. Any medical condition present at the initial study day (birth day), which remains unchanged or improves, should not be recorded as an adverse event at subsequent examination / sampling days. However, if there is **deterioration** of a medical condition that was present at the initial study day (birth, day 0), this should be considered a **new** adverse event and reported. This information is collected by examining the subject. Ongoing adverse events at the final study day should be followed until the event is resolved or remains stable.

Clinically significant changes (abnormalities), in the judgment of the investigator, in physical examination from the baseline exam will be recorded as an adverse event.

The following information must be collected and recorded for each AE:

- AE term (diagnosis)
- Start date of AE
- Stop date of AE
- Severity of AE (mild, moderate, or severe)
- Seriousness of AE (serious or non-serious)
- Action taken regarding study medication (none, study medication dose reduced, study medication interrupted, or study medication stopped);
- Action taken regarding AE
- AE outcome (resolved, ongoing, death, or lost to follow-up)
- AE causality (not related, possibly related, related)

The investigator should determine study drug relationship for each adverse event. AEs occurring prior to administration of the study drug will be considered as not related to the study drug. The Investigator will be using the following explanations for assessment of causality:

#### **Not related**

- The event is clearly related to other factors such as the subject's clinical state, therapeutic interventions, or concomitant drugs administered to the subject.

#### **Possibly Related**

- The event follows a reasonable temporal sequence from the time of drug administration,
- And/or follows a known response pattern to the trial drug,
- **But** could have been produced by other factors such as the subject's clinical state, therapeutic interventions, or concomitant drugs administered to the subject.

#### **Related**

- The event follows a reasonable temporal sequence from the time of drug administration,
- **And** follows a known response pattern to the study drug,
- **And** cannot be reasonably explained by other factors such as the subject's clinical state, therapeutic interventions, or concomitant drugs administered to the subject,
- **And** either occur immediately following trial drug administration, **or** improves on stopping the drug, **or** reappears on repeat exposure, **or** there is a positive reaction at the application site.

Severity of an adverse event is defined as a qualitative assessment of the degree of intensity of an adverse event as is determined by the investigator or reported to him/her by the subject.

The assessment of severity is made irrespective of drug relationship or seriousness of the experience and should be evaluated according to the following scale:

- 1. Mild**– The adverse event is easily tolerated.
- 2. Moderate**– The adverse event is not easily tolerated.
- 3. Severe**– The adverse event is incapacitating and the subject is unable to function.

It is up to the discretion of the Investigator, in the event of an AE or SAE, to temporarily discontinue study medication or to discontinue the subject from the study. The end of study examinations / samplings must be performed if the subject is discontinued from the study.

## **9.2 Reporting Serious Adverse Events**

A serious adverse event (SAE) is defined as any adverse drug experience occurring at any dose that results in any of the following outcomes:

- Results in death,
- Is life-threatening (NOTE: The term "life-threatening" in the definition of "serious" refers to an event in which the subject was at risk of death at the time of the event; it does not refer to an event which hypothetically might have caused death if it was more severe),
- Results in inpatient hospitalization or prolongation of existing hospitalization,
- Results in a persistent or significant disability/incapacity, or
- Results in a congenital anomaly/birth defect.

Important medical events that may not result in death, be life-threatening, or require hospitalization may be considered a serious adverse drug experience when, based upon appropriate medical judgment, the event may jeopardize the subject and may require medical or surgical intervention to prevent one of the outcomes listed in this definition. Examples of such events include allergic bronchospasm requiring intensive treatment in an emergency room or at home, blood dyscrasias or convulsions that do not result in an inpatient hospitalization, or the development of drug dependency or drug abuse.

Any SAE occurring during the study (from receiving informed consent until end of study) or within 30 days after study completion will be reported to the Sponsor within 24 hours of knowledge of the event.

Initial SAE reporting can be done by telephone with written reports to follow by fax within 24 hours.

### **Sponsor Safety Contact Information**

Contact: [name]  
Title: MD Professor  
Address: The Queen Silvia Children's Hospital  
Göteborg University/Östra  
[name]  
24 hour line: [name]  
Office: [name]  
[contact]

All SAEs must be followed until resolution (subject has returned to baseline status of health), or until stabilization (the investigator does not expect any further improvement or worsening of the reported event).

Some events may require immediate reporting to the appropriate regulatory authorities. The Sponsor is responsible for regulatory reporting. Events that are life-threatening, result in a subject's death, or are considered related to the use of the study drug and unexpected according to the current approved product information for the investigational product (SUSARs) must be reported to the appropriate regulatory authorities by fax or telephone within 7 days. A written report must follow within 15 days after the initial notification. All other SAEs that are considered related to the use of study drug and are not unexpected (per the current approved product information) will be reported according to ICH guideline, E2F-Note for guidance on development safety update reports, to the authorities once a year.

The Sponsor is responsible for notifying the MPA and REG of all SUSARs that occur in the study. The Sponsor has an agreement with Pharma Consulting Group in Uppsala AB (PCG), [name]. Any SAE occurring in the study will be reported to PCG who will determine if the SAE is a SUSAR or not. PCG will classify the SAE as a SAE or a SUSAR and report the event to the Eudravigilance database, coded according to MedDRA.

The Sponsor will provide data related to any AE deemed to be related or possibly related to SMOFlipid® administration to Fresenius Kabi AB within 7 days. All SAEs occurring in the study should be reported to Fresenius Kabi AB within 24 hours after the Sponsor receive knowledge of the event. The SAE Report Form should be completed according to the guidelines and faxed to Fresenius Kabi AB.

## **10 STUDY MANAGEMENT**

### **10.1 Subject Discontinuation**

A discontinuation occurs when an enrolled subject ceases participation in the study, regardless of the circumstances, prior to completion of the protocol.

The investigator has the right to remove a subject at any time if it is in the best medical interest of the subject.

Subjects will be discontinued from treatment prior to completion for any of the following reasons:

- Consent withdrawn / the parents/guardians wish to discontinue study treatment
- AE (clinical events or laboratory values) that contraindicate continuing the study.
- Best interest of the patient, as judged by the Investigator
- Protocol violation

- Administrative Decision
- Other, by Investigator specified reason

Subjects withdrawn from the study for a SAE should be followed until the SAE has resolved. Appropriate supportive and/or definitive therapy should be administered as required.

The investigator must determine the primary reason for discontinuation. The reason for a subject discontinuing from the study will be recorded on the case report form. Withdrawal due to an adverse event should be distinguished from withdrawal due to other reasons, according to the definition of an adverse event noted earlier. A discontinuation must be reported immediately to the Kabi Fresenius AB safety monitor or his/her designated representative if it is due to an adverse event. The **End of Study** examination / sampling must be performed at the time of the study discontinuation. The investigator will record the reason for study discontinuation, provide or arrange for the appropriate follow-up (if required) for such subject, and document the course of the subject's condition.

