### **11.1 Determination of Sample Size and Statistical Methods**

#### **Primary endpoint**

The primary endpoint is ROP classified as 0,1,2,3,3+ which is the expected possible range of ROP stages that will be encountered in the study based on analysis of infants screen for ROP in Gothenburg through the years 2004 to 2008. This is an ordinal scale with higher numbers indicating a more severe outcome. The proportion of children with each outcome based on register data is given in table below. In this table an anticipated treatment effect is also indicated by presenting expected outcome in the treated group.

| ROP  | 0 | 1 | 2 | 3 | 3+ | Total |
|-------------|----------|----------|----------|----------|-----------|--------------|
| Control (%) | 26       | 15       | 24       | 18       | 17        | 100          |
| Active (%)  | 49       | 19       | 19       | 9        | 4         | 100          |

Percentage distribution of children with different ROP-outcomes. Control group based on register data and active group based on expected treatment effect.

The estimated treatment effect is based on the following assumptions.

- 25 % of the children will not have any benefit from the treatment.
- 25% will have their ROP reduced one step (e.g. from 2 to 1)
- 50% will have their ROP reduced two steps. (e.g. from 3+ to 2)

The null hypothesis to test is if the distribution ( $F$ ) of ROP ( $X$ ) is the same in both treatment groups.

$$H_0 : F_C(X) = F_A(X)$$

$$H_1 : F_C(X) \neq F_A(X)$$

This hypothesis will be tested with the Mann-Whitney test.

In order to have 80% power at a significance level of 5% a sample of 40 subjects per group is needed (80 subjects in total).

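### Section 10.1 merges stopping the study lipid with leaving the study, so an infant discontinued before the first eye examination can be closed out without the primary outcome, though routine screening will still produce it

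*Protocol*

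**What the plan says.** Section 10.1 opens by defining a discontinuation as an enrolled subject ceasing to take part in the study, for whatever cause. The list that follows is introduced differently: "Subjects will be discontinued from treatment prior to completion for any of the following reasons". Its reasons include an adverse event, a protocol violation, an administrative decision and the investigator's judgement. Its first entry puts withdrawn consent and a parental wish to stop study treatment on one line. The section then says that the End of Study "examination / sampling must be performed at the time of the study discontinuation". Section 9.1 repeats the rule for adverse events: "The end of study examinations / samplings must be performed if the subject is discontinued from the study".

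The primary endpoint (11.1) is ROP stage on the scale 0, 1, 2, 3, 3+, and "This hypothesis will be tested with the Mann-Whitney test". On timing, 8.1 says "The retinal examination will be performed once weekly starting at five to six weeks of age" and the Table 1 footnote agrees, while 6.3 says four to five weeks. Screening is weekly and part of clinical routine (section 4).

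After discontinuation, 10.1 asks for three things: follow-up of a serious adverse event until it resolves, appropriate follow-up if required, and a record of the course of the subject's condition. None of these is tied to ROP or to 40 postmenstrual weeks. Section 11.2 allows non-evaluable subjects to be left out of the summary statistics. Section 5.1 raises 80 subjects to 90 to cover violations and withdrawals.

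**The concern.** Stopping a treatment and leaving a trial are different events. Section 10.1 gives reasons for the first and attaches the consequences of the second. A site that follows it literally does the End of Study examination when an infant is taken off the study lipid and then stops recording. If that happens before four to six weeks of age, no ROP stage exists yet.

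The loss is avoidable. The infant would be expected to stay in the weekly screening programme, so the result will normally exist in the clinical record. But 6.3 and 11.4 describe the examining ophthalmologists as unaware of which infants are in the study, so a result reaches the trial only if study staff collect it. No section asks them to do so for a discontinued infant.

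Two things are at stake. One is power, which over-recruitment can restore. The other is bias, which it cannot. The only blinding described is that of the ROP assessment (6.3), so decisions to stop may be made knowing the arm, and the losses could differ between arms in number and in severity.

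**Working it through.** **1. The texts side by side.**
- Definition (10.1): leaving the study.
- Listed reasons (10.1): for being taken off treatment.
- Consequence (10.1, 9.1): End of Study examination at that time.
- First eye examination: 4 to 5 weeks (6.3) or 5 to 6 weeks (8.1, Table 1).
- Duty to collect ROP results after discontinuation: none stated.

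So for any discontinuation before about 4 to 6 weeks, the protocol's own schedule gives no primary outcome at close-out.

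**2. The plan's own sample size.** Inputs from 11.1: control distribution 26/15/24/18/17%, active 49/19/19/9/4%, two-sided 5%, 80% power, 40 per group. The tie-corrected Mann-Whitney test was simulated with 40,000 runs per setting.
- 40 per group: power 0.79, which agrees with the stated 80% to within about a point.
- Allowance in 5.1: 80 / (1 − 10/90) = 90, which also agrees.

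The sample size is not in question here.

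**3. Cost in power if losses are unrelated to ROP.** The protocol gives no discontinuation rate, so these equal losses from 45 per arm are assumptions.

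| Assumed loss | Left per arm | Power |
|---|---|---|
| 0% | 45 | 0.84 |
| 5% | 43 | 0.82 |
| 10/90 = 11% | 40 | 0.79 |
| 15% | 38 | 0.76 |
| 20% | 36 | 0.74 |
| 30% | 31 | 0.68 |

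**4. False-positive rate.** The control distribution was used in both arms (no true effect), 45 randomised per arm, and lost infants left missing. All splits are assumptions.

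| Lost (one arm / other arm) | Losses unrelated to ROP | All lost infants at stage 2 or more |
|---|---|---|
| 5 / 5 | about 5% | 5 to 6% |
| 7 / 3 | about 5% | 6 to 8% |
| 8 / 2 | about 5% | 9 to 10% |
| 5 / 0 | about 5% | 7 to 8% |
| 8 / 0 | about 5% | 11 to 12% |
| 10 / 0 | about 5% | 15 to 17% |

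The ranges cover separate simulation runs and two ways of modelling the loss: removing infants directly from those simulated at stage 2 or more, or reducing the probabilities of those stages. The last three rows are the extreme case, in which one arm alone loses infants and all of them have moderate or severe disease.

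**The case against.** Much can be said for the protocol. The End of Study examination is triggered by discontinuation from the study, and 9.1 separates temporarily stopping study medication from discontinuing the subject. The adverse event form in 9.1 also has a category for study medication stopped. Section 10.1 leaves some room for recording through its appropriate-follow-up clause. Routine ROP results may be retrievable later, and the analysis of missing outcomes is usually left to the SAP. All of this lowers the severity. It does not remove the gap: no section describes a permanent lipid stop with follow-up continuing, and an SAP cannot analyse results that were never collected.

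Three stronger readings are tempting, and the documents do not support them.

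- **That an infant closed out early would be scored stage 0.** No section says so. Section 10.4 says that an assessment not done and not going to be available is entered as N/D. False-positive rates computed from stage-0 scoring therefore do not apply.
- **That 10 of 90 infants would be lost this way.** The allowance in 5.1 covers violations and withdrawals of every kind and at any time, including infants already examined and families who withdraw consent. It does not count early treatment stops.
- **That most discontinuations would fall in the first two weeks.** The 7 to 10 days in 6.2 describe the build-up of enteral feeding. The same section expects longer parenteral feeding in some of the most immature infants, and Table 1 and 6.2 allow it to 36 weeks postmenstrual age. For an infant born before 28 weeks that is more than 36 − 28 = 8 weeks after birth, later than the first eye examination. A short lipid course that ends as planned is not a discontinuation at all.

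**Conclusion.** The point holds as a defect of wording with a real but unquantified effect, and it should be fixed. Section 10.1 runs two events together, and an infant discontinued before about 4 to 6 weeks can leave the trial without a primary outcome that routine care would still provide.

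The size depends on what the documents do not state: how many infants are discontinued early, in which arm, and whether the stop is related to later ROP. With losses that are unrelated to ROP or balanced, the test keeps a false-positive rate near 5% and only power is lost. A clear inflation, to about 8 to 15%, needs 5 to 10 losses confined to one arm with every lost infant at stage 2 or more. That is an upper illustration and not a forecast. Where parents withdraw consent to data collection, the loss may be unavoidable under any wording.

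**What to change.** Amend 10.1 and 9.1 to distinguish two events.

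- **(a) Study lipid stopped, for any reason.** The infant's routine ROP examinations, growth measurements and adverse events continue to be recorded on the original schedule to 40 postmenstrual weeks. This is a rule about data collection only. It leaves unchanged the investigator's right to stop treatment or to remove a subject from study procedures, and it does not touch the clinical rules for stopping.
- **(b) Consent to data collection withdrawn.** The parents are asked whether routine ROP screening results may still be used, and their answer is recorded.

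The combined first entry in the 10.1 list should be split to match. The start of ROP screening in 6.3 should be reconciled with 8.1 and Table 1, so that it is clear from what age an outcome can exist. No separate rule against scoring an unexamined eye is needed, because 10.4 already covers it.

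The cost is a wording amendment, matching text in the parent information and CRF instructions, and some extra CRF follow-up for the infants concerned. No new examinations are needed, because weekly screening and growth measurement are already scheduled.
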